## Abstract

**Background:**

Branched-chain amino acids (BCAAs) are essential amino acids for protein metabolism. Preclinical research in mice suggested that BCAA intake relative to other amino acids, in the context of a high-carbohydrate diet, was associated with hyperphagia, obesity, and reduced lifespan. These effects were not attributed to BCAAs alone, nor did they manifest through canonical mechanistic target of rapamycin–insulin-like growth factor 1 pathways; rather, they resulted from indirect effects of other amino acids, notably tryptophan, on appetite. As population aging and obesity-related chronic diseases present significant public health challenges, understanding appetite regulation is critical. To date, no clinical trial has examined the effects of BCAAs on appetite regulation in older adults. On the basis of our preclinical results, we hypothesized that, compared to the control diet, a diet supplemented either with BCAA or with BCAAs and methionine would increase appetite and energy intake, whereas supplementation with BCAA and tryptophan would not increase appetite.

**Objective:**

We aimed to translate these preclinical findings to humans by examining the effects of BCAAs per se and in combination with tryptophan and methionine on appetite and other health measures in a cohort of older participants.

**Methods:**

This randomized controlled clinical trial recruited 110 adults (aged 65-80 y; BMI 20-35 kg/m^2^). Participants were randomly allocated to four 4-week intervention groups: (1) control (no supplementation), (2) BCAAs, (3) BCAAs+tryptophan, or (4) BCAAs+methionine. All participants received a controlled diet, with intervention groups additionally receiving amino acid supplements. The primary outcomes are appetite assessed via self-reports and fibroblast growth factor 21 levels (a marker of protein appetite), and energy intake quantified from dietary intake data. Secondary outcomes include body composition, cardiometabolic health, gut microbiota, blood biomarkers, sleep, and physical performance. Descriptive statistics will be used to summarize participant characteristics. Linear mixed models will assess intervention effects, with and without adjustment for relevant covariates. Diet-specific self-reported appetite and palatability scores will be analyzed using generalized additive mixed models.

**Results:**

The trial was registered on April 12, 2021. Recruitment commenced in April 2022 and was completed in November 2025, with 308 individuals screened and 100 completing the study. Data analyses are planned for completion by December 2026, with results expected to be published in 2027. Data cleaning and analysis are currently in progress and are expected to be completed by December 2026, with trial results expected to be published in 2027.

**Conclusions:**

This study will clarify the effects of BCAAs, either alone or in combination with tryptophan or methionine, on appetite and related outcomes in an older population. The findings may inform nutritional strategies targeting appetite regulation and metabolic health to support healthy aging.

## Introduction

Population aging represents one of the major global public health challenges. It has been estimated that by 2030, 1 in 6 people in the world will be aged ≥60 years [1]. With population aging, the prevalence of obesity-related chronic diseases is also rising, including type 2 diabetes, cardiometabolic diseases, obesity, and sarcopenia [2]. These conditions significantly impact quality of life and health care costs. Dietary interventions involving supplementary food products have been prominently highlighted in research over the past decades and, in some cases, have demonstrated positive effects in supporting metabolic health and healthy aging [3-5].

Protein is composed of amino acids (AAs) that impact all aspects of metabolism, growth, development, and aging [6]. Accordingly, many organisms regulate the intake and metabolism of protein, with a specific appetite for protein representing an important determinant of feeding behavior. It has been shown that many species, including humans, consume more energy when dietary protein is diluted by fats and carbohydrates, a phenomenon known as protein leverage, thereby increasing the risk of weight gain, obesity, and adverse health outcomes [7,8]. Although a low concentration of dietary protein increases the risk of deleterious health consequences through increased food and energy intake, excess protein intake has also been shown to have detrimental effects. High dietary protein, especially when associated with low intake of healthy carbohydrates, increases markers of aging in model organisms, such as mechanistic target of rapamycin (mTOR) and insulin-like growth factor 1 (IGF-1), especially during midlife [9,10]. Additionally, it has been demonstrated that changes in the dietary ratio of protein to carbohydrate impact several health markers including reproduction, immune function, microbiome, and late-life cardiometabolic health [9,11].

Essential AAs are 9 of the 20 AAs that must be obtained through the diet [12]. The branched-chain AAs (BCAAs; ie, valine, leucine, and isoleucine) are well known for their established anabolic and anticatabolic effects on skeletal muscle protein metabolism. These properties have made BCAA supplementation attractive to athletes and older adults, who commonly experience anabolic resistance and age-related loss of lean body mass. By contrast, circulating levels of BCAAs have also been considered predictors of developing type 2 diabetes, insulin resistance, and obesity [13,14]. Although elevated BCAA levels are associated with increases in canonical markers of aging, such as mTOR and IGF-1, this occurs primarily when BCAAs are provided against a low-carbohydrate background [9].

In mice, it was found that when BCAAs were increased in the diet within a fixed protein complement against a high-carbohydrate background, this resulted in hyperphagia, obesity, and reduced lifespan [15]. However, these effects were not associated with BCAA-activating proaging nutrient-sensing pathways such as mTOR, but rather were due to indirect effects on appetite control mediated by other AAs within the protein complement. It was found that selectively increasing dietary tryptophan and threonine, but not methionine, prevented hyperphagia under high-BCAA intake. Increasing the proportion of BCAAs within the fixed complement of dietary protein inevitably increased the ratio of BCAAs with respect to other AAs. Because BCAAs and tryptophan share an AA transporter (L-type AA transporter 1) for entry into the brain, competition from elevated BCAA with tryptophan led to a reduction in brain tryptophan concentrations, reduced serotonin levels, and consequently increased appetite signaling [15-17].

Fibroblast growth factor 21 (FGF-21) is a peptide hormone involved in metabolic homeostasis and is predominantly produced by the liver [18]. FGF-21 is the first known hormone signal for low protein status, being elevated in circulation under low-protein conditions. A high-carbohydrate, low-protein diet has been shown to boost levels of FGF-21. Perfusion of FGF-21, either centrally or peripherally, results in mice selecting a higher protein intake, indicating its primary role in the control of protein appetite [19].

To date, human studies of BCAA supplementation have primarily focused on metabolic health, muscle protein synthesis, liver disease, and neurological or sleep-related outcomes, demonstrating the feasibility and safety of BCAA interventions [20-24], while the effect of BCAA, alone or in combination with other AAs, on appetite regulation in older adults remains largely unexplored. This gap is clinically important: aging is associated with the “anorexia of aging” (contributing to malnutrition) as well as dysregulated appetite responses that trigger conditions such as sarcopenic obesity [25,26].

Our aim in this trial is to translate the preclinical work from aging mice to humans aged 65 to 80 years by supplementing a standard control diet (18%-19% of energy from protein, 30%-35% from fat, and 45%-65% from carbohydrates) with BCAA alone or in combination with either tryptophan or methionine. We hypothesize that, compared to the control diet, participants receiving a diet supplemented with BCAAs alone or BCAAs in combination with methionine will have increased appetite and energy intake, whereas supplementation with BCAAs and tryptophan will mitigate these effects.

## Methods

### Study Design

The Optimizing Diet for Better Health (OptHealth) study is a randomized clinical trial (RCT) with a total target sample of 110 participants and 100 completers. The sample size was determined by circulating FGF-21 levels (pg/mL), using a 2-tailed ANOVA design and assuming an SD of 70 [18], 80% power, and an α of .05; a difference of 30% (control group mean 149.4 pg/mL) [27] may be detected with a sample size of 25 participants per group (100 in total). The dropout rate was estimated to be 10%; therefore, 110 participants were recruited. Clinical assessments were performed prior to initiating the intervention and after the 4-week intervention period (Figure 1). All study visits were conducted at the Charles Perkins Centre (CPC)–Royal Prince Alfred Hospital (RPAH) clinic. This study protocol was prepared in accordance with the SPIRIT (Standard Protocol Items: Recommendations for Interventional Trials) guidelines for RCTs [28] (Checklist 1).

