### Randomization and Intervention

Enrolled participants were randomized to 1 of 4 treatment groups using permuted block randomization. Random blocks of 4 were generated using the R package “blockrand” [32] for male and female participants separately. Allocation was concealed using sealed, opaque, numbered envelopes. The study coordinators and participants were not blinded to group allocation.

Participants randomized to intervention groups were provided with supplements to be taken with their meals (Table 2). Participants in the BCAA group (group B) were instructed to consume 1 capsule of BCAA supplements thrice daily with their main meal. Participants in the BCAA and tryptophan group (group C) were instructed to consume 1 capsule of BCAA thrice daily and 1 tablet of tryptophan supplement twice daily. Participants in the BCAA and methionine group (group D) were instructed to consume 1 capsule of BCAA and 1 capsule of methionine supplement thrice daily.

**Table 2. T2:** Description of diets and interventions for study groups.

Diet name or group	Diet or intervention description
Group A: control	Regular diet containing 18% to 19% of total energy from protein
Group B: BCAA^a^	Regular diet+3 doses of BCAAs (L-leucine 300 mg, L-isoleucine 150 mg, and L-valine 150 mg)
Group C: BCAA+tryptophan	Regular diet+3 doses of BCAAs (L-leucine 300 mg, L-isoleucine 150 mg, and L-valine 150 mg)+2 doses of L-tryptophan (1000 mg)
Group D: BCAA+methionine	Regular diet+3 doses of BCAAs (L-leucine 300 mg, L-isoleucine 150 mg, and L-valine 150 mg)+3 doses of L-methionine (500 mg)

a BCAA: branched-chain amino acid.

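### The stated inputs do not give 80% power for a 30% FGF-21 difference with 25 per group: the unadjusted four-group ANOVA reaches 75% at best, and one arm versus control about 60%

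*Protocol article*

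**What the plan says.** The Study Design section of the protocol article contains the only sample-size calculation. It is based on circulating FGF-21, "using a 2-tailed ANOVA design and assuming an SD of 70 [18], 80% power, and an α of .05". The target effect is "a difference of 30% (control group mean 149.4 pg/mL"), which "may be detected with a sample size of 25 participants per group (100 in total"). The allowance for losses follows: "The dropout rate was estimated to be 10%; therefore, 110 participants were recruited". The Randomization and Intervention section confirms four arms: "Enrolled participants were randomized to 1 of 4 treatment groups using permuted block randomization".

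The Statistical Analysis section plans a one-way ANOVA of follow-up values across the four groups. It then plans a linear model of follow-up adjusted for baseline (model 1) and a further model with covariates (model 2). Dropouts are excluded. The sample-size text gives no pattern of group means, no correlation between baseline and follow-up, and no pooled contrast.

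**The concern.** All the inputs to the calculation are printed, so it can be checked as it stands. A difference of 0.64 SD with 25 per group is small for a claim of 80% power, whether the test is a 3-df ANOVA or a comparison of two arms.

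FGF-21 is one of the measures of the primary outcome. The Strength and Limitations section also relies on it as an objective measure in an open-label trial. If FGF-21 shows no difference, readers will judge that result against the stated 80%. A figure that does not follow from its inputs would make the result look more informative than the stated calculation allows.

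**Working it through.** **Inputs, all from Study Design.** Control mean 149.4 pg/mL; difference 30%; SD 70; two-sided α .05; 25 per group in four groups; stated power 80%.

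**Effect size.** Δ = 0.30 × 149.4 = 44.82 pg/mL. d = 44.82 / 70 = 0.640, and d² = 0.410.

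**Four-group ANOVA (the test named).** Power comes from the noncentral F distribution with 3 and 96 df, critical value 2.70. The noncentrality is λ = n Σ(μᵢ − μ̄)² / SD². The text fixes the size of the difference but not where the other arms lie, so I took every pattern whose largest difference between two groups is Δ. Within that range Σ(μᵢ − μ̄)² is largest, at Δ², when two arms lie at each end. It is smallest, at Δ²/2, when two arms lie exactly midway. The first and last rows are therefore the bounds.

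| Pattern of means | Σ(μᵢ − μ̄)² | λ at n = 25 | Power | n per group for 80% | Difference detectable with 80% power at n = 25 |
|---|---|---|---|---|---|
| Two arms 30% above the other two | Δ² | 25 × 0.410 = 10.25 | 75.4% | 28 | 31.6% |
| One arm differs from the other three | ¾Δ² | 18.75 × 0.410 = 7.69 | 61.5% | 37 | 36.5% |
| Two extremes, two arms midway | ½Δ² | 12.5 × 0.410 = 5.12 | 43.4% | 55 | 44.7% |

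The stated 80% is not reproduced by any pattern with a 30% range. Even the most favourable one needs 28 per group, or 112 completers rather than 100.

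**One arm versus control, unadjusted.** Noncentrality = d × √(25/2) = 0.640 × 3.536 = 2.264. Power is 60.2% with 48 df and 61.1% with the pooled 96 df. For 80%, 40 per group are needed by the t test. With 25 per group the difference detectable with 80% power is 56.6 pg/mL, and 56.6 / 149.4 = 37.9%.

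**Readings that might restore 80%.**
- A one-sided comparison of one arm with control gives 72.1%, and the text says two-tailed.
- Control against the three supplement arms pooled (25 v 75) gives 78.4%. No such contrast is stated, and it conflicts with the expectation that the tryptophan arm behaves differently.
- Two arms pooled against two (50 v 50) gives 88.7%, but this too is not stated.
- With 25 per group, the SD that would give 80% is 66.5 for the best ANOVA pattern and 55.4 for one arm versus control, against the stated 70.

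**Baseline adjustment.** With correlation r between baseline and follow-up, the residual SD is about 70 × √(1 − r²). Setting this equal to the SDs just given:
- Best ANOVA pattern: r = √(1 − (66.5/70)²) = 0.31.
- One arm versus control: r = √(1 − (55.4/70)²) = 0.61.

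At r = 0.5 the powers are 87.4% and 72.6% respectively. The protocol article states no r.

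**Dropout.** 100 / 0.9 = 111.1, so 112 after rounding up, against 110 recruited. This is not at issue.

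**The case against.** The strongest counter-argument is that the shortfall is small where it matters most. If BCAA and BCAA+methionine both raise FGF-21 by 30% and the tryptophan arm stays at control level, power is 75% and the detectable difference is 31.6% rather than 30%. The 43% figure comes from a pattern that nobody proposes. Arm-versus-control tests are not the test named in the calculation.

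Part of this stands. The 43% is a lower bound and should be presented as one, and the pairwise figure is a second reading. But even the favourable pattern misses 80%, and it is an inference. The hypotheses concern appetite and energy intake, not FGF-21 levels. The Abstract expects no increase with tryptophan, while the Introduction says only that it will mitigate the effect. If tryptophan halves the effect (means 0, Δ, Δ/2, Δ), ANOVA power is 57% and 40 per group are needed. The pairwise reading is also reasonable, because the effect is expressed relative to the control mean.

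A reader might go further and infer that the trial itself has only about 60% power, or that it will miss a true 30% difference from control about 40% of the time. The document does not support that. Those figures hold only for unadjusted follow-up values. The Statistical Analysis section already plans a baseline-adjusted model, whose power depends on an unstated correlation and may be above or below 80%.

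The full protocol may contain a pattern of means or a correlation. That would not make the calculation printed here, described as an ANOVA with SD 70, come out at 80%.

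**Conclusion.** The stated power is wrong as written. With the document's own inputs, the unadjusted four-group ANOVA has 43% to 75% power for a maximum difference of 30%, and an unadjusted comparison of one arm with control has about 60%. The shortfall in group size is 3 per group at best (28 v 25) and 15 per group for one arm versus control (40 v 25).

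This rests on taking 149.4 as the control mean, 30% as the largest difference between any two groups, a common SD of 70, and 25 analysed per group. It concerns the printed calculation. It does not show that the planned baseline-adjusted analysis is underpowered; that power cannot be determined from the document.

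**What to change.** Enrol no one. Replace the power statement with one labelled as unadjusted, for example:

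> With 25 per group, SD 70 and α .05, the unadjusted four-group ANOVA has 43–75% power for a maximum difference of 30%, depending on the pattern of means, and 80% power for a difference of about 32% at best. An unadjusted comparison of one arm with control has about 60% power for 30%, and 80% power for about 38% (57 pg/mL).

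Add that the planned baseline-adjusted model will have higher power, by an amount that depends on the correlation between baseline and follow-up, for which no value was assumed. Do not choose a correlation or a pooled contrast now to recover 80% at 30%. Recruitment and outcome collection are complete, so that would fit the justification to the result wanted.

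The cost is wording only, and the stated figure becomes less favourable. No analysis or study procedure changes. Results are expected in 2027, so the correction can be made before they are interpreted.

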**Figure 1. F1:**
[figure not shown]
CONSORT (Consolidated Standards of Reporting Trials) flow diagram of participant recruitment, randomization, and analysis. BCAA: branched-chain amino acid.

### Eligibility Criteria

Trial inclusion and exclusion criteria are presented in Textbox 1.

The exclusion criteria were selected to minimize confounding effects on appetite regulation, energy intake, and metabolic outcomes and also to ensure participant safety and protocol compliance. Individuals with metabolic, endocrine, hepatic, renal, or malignant conditions were excluded due to their potential influence on appetite, protein metabolism, and cardiometabolic biomarkers. Individuals with known disorders of BCAA metabolism, such as maple syrup urine disease, were excluded due to their altered BCAA metabolism and potential safety concerns associated with BCAA supplementation [29]. Participants using medications known to affect body weight, appetite, or energy expenditure were excluded to reduce pharmacological confounding. Specifically, individuals who had used antibiotics within 4 weeks prior to study commencement were excluded due to their potential impact on gut microbiota and related outcomes. Individuals with recent unintentional weight loss, current smoking, or high alcohol intake were excluded due to their independent effects on appetite regulation and metabolic health. Participants following restrictive dietary patterns or with food allergies or intolerances that would limit adherence to the provided study diet were excluded to ensure dietary intervention standardization.

Textbox 1.Inclusion and exclusion criteria for the Optimizing Diet for Better Health study.
**Inclusion criteria**
Male participants and female participants (at postmenopausal stage) aged 65 to 80 yearsBMI of 20 to 35 kg/m^2^Access to and ability to operate a smartphone (running iOS or Android)Ability to provide informed consent and to undergo all study assessments
**Exclusion criteria**
Diagnosis of diabetes mellitus (insulin-dependent; type 1 or type 2), renal or liver disease, cancer or active neoplasms, untreated or uncontrolled hyperthyroidism, schizophrenia, or sleep apnea or known disorders of branched-chain amino acid metabolism (maple syrup urine disease)Use of antibiotics or other medications known to affect weight or energy expenditure within the 4 weeks prior to baseline assessmentUnintentional weight loss of >10% body weight within the past 5 yearsCurrent smokingAlcohol intake of >3 standard drinks per day or unwillingness to refrain from alcoholAdherence to a vegan and vegetarian diet, strict dietary restrictions, food allergies and/or intolerances, and contraindications to dietary changes as determined by a treating physician

### Recruitment

Participants were recruited via flyers, the University of Sydney website, community and library engagement events, senior fitness classes, and word of mouth. Interested individuals contacted the research team via phone call or email. A prescreening assessment was conducted over the phone to determine their initial eligibility. Those who meet the criteria were invited to attend a face-to-face screening interview at the CPC-RPAH clinic.

### Screening and Consent

During the screening visit (visit 1), potential participants were asked questions to gather information on sociodemographic characteristics, medical history, medication use, smoking, and alcohol consumption. The screening interview was conducted by a study investigator (research dietitian), who provided all the information related to baseline and final assessments, including information about blood, stool, and urine sample collection; weighed food diary completion; and use of a wrist-worn device to measure physical activity level and sleep quality and duration. Written informed consent was obtained from participants who chose to enroll in the study.

### Baseline and Final Assessment

Following the screening interview, participants attended another 2 clinical assessment visits (visits 2 and 3), during which several health-related measurements were taken. Details on the schedule of visits and health assessments are outlined in Figure 2.

**Figure 2. F2:**
[figure not shown]
Schedule of visits and testing procedures at the Charles Perkins Centre Royal Prince Alfred Hospital clinic of Optimizing Diet for Better Health study. WFR: weighted food record.

### Diet

During the 4-week intervention period, participants were provided with ad libitum access to a standard diet containing 18% to 19% of energy from protein, 30% to 35% from fat, and 45% to 65% from carbohydrates, as per the Acceptable Macronutrient Distribution Ranges set by the National Health and Medical Research Council [30]. Participants were allowed to consume additional nonstudy foods, including milk (up to 100 ml a day), nonstarchy vegetables (up to 2 cups a day), and fresh fruit (up to 2 servings a day). A bottle of 1 L of olive oil was given to participants for salad dressing.

The number of serves of core food groups within the study diet is displayed in Table 1. The prescribed study diet provided approximately 6700 kJ per day, supplying 85 g of protein, 45 g of fat, and 200 g of carbohydrates (detailed nutrition profile is provided in Multimedia Appendix 1). When including the permitted nonstudy foods, the total daily food provision was estimated to provide approximately 8200 to 8700 kJ per day, with corresponding macronutrient availability of approximately 90 to 93 g of protein, 60 to 75 g of fat, and 240 to 250 g of carbohydrates. All calculations were performed using FoodWorks 10 Professional for Windows (Xyris Software Pty Ltd) [31].

**Table 1. T1:** Servings of food groups provided in the study diet.

Food group	Study diet (serves)
Grains	6.2
Whole grains	2.5
Other grains	3.7
Fruit	1.1
Vegetables	6.6
Legumes	0.1
Other vegetables	6.5
Diary	1.6
Milk	0.7
Cheese	0.3
Yoghurt	0.6
Protein foods	1.6
Red meats	0.9
Poultry	0.5
Eggs	0
Seafood	0.1
Nuts or seeds	0.1
Legumes protein	0
Oil equivalents (tsp)^a^	4

a LC n-3, long chain omega-3 fatty acids; tsp: teaspoon; oil equivalent: the amount of dietary fat or oil represented in the Australian Dietary Guidelines. One oil equivalent is typically equal to 10 grams of fat.

